## Abstract

**Background:** There is ample evidence of the high mental health burden caused by Inflammatory Bowel Disease (IBD). Several constructs such as experiential avoidance, cognitive fusion, shame, and self-criticism have recently emerged as potential intervention targets to improve mental health in IBD. Psychotherapeutic models such as Acceptance and Commitment Therapy and compassion-based interventions are known to target these constructs. In this protocol, we aim to describe a two-arm Randomized Controlled Trial (RCT) testing the efficacy of an ACT and compassion-focused intervention named Living with Intention, Fullness, and Engagement with Inflammatory Bowel Disease (LIFEwithIBD) intervention + Treatment As Usual (TAU) vs. TAU in improving psychological distress, quality of life, work and social functioning, IBD symptom perception, illness-related shame, psychological flexibility, self-compassion, disease activity, inflammation biomarkers, and gut microbiota diversity.

**Methods:** This trial is registered at ClinicalTrials.gov (Identifier: NCT03840707, date assigned 13/02/2019). The LIFEwithIBD intervention is an adaptation to the IBD population of the Mind programme for people with cancer, an acceptance, mindfulness, and compassion-based intervention designed to be delivered in a group format. The LIFEwithIBD intervention's structure and topics are presented in this protocol. Participants were recruited at the Gastroenterology Service of the Coimbra University Hospital between June and September 2019. Of the 355 patients screened, 61 participants were selected, randomly assigned to one of two conditions [experimental group (LIFEwithIBD + TAU) or control group (TAU)] and completed the baseline assessment. Outcome measurement took place at baseline, post-intervention, 3- and 12-month follow-ups.

**Discussion:** Results from this RCT will support future studies testing the LIFEwithIBD intervention or other acceptance and/or compassion-based interventions for IBD.

## Introduction

Inflammatory bowel disease (IBD) is a group of chronic conditions comprised mainly of Crohn's disease and ulcerative colitis and characterized by inflammation of the intestinal tract, usually leading to symptomatology such as diarrhea, abdominal pain, rectal bleeding, fatigue, and weight loss. IBD comprises periods of active disease, with increased symptomatology, alternating with periods of remission, in a usually unpredictable manner (1). People living with IBD are faced with significant disease burden (2–4), with impaired daily functioning (5), and are at risk of developing anxiety and depression disorders (6, 7). During periods in which symptoms are present (active disease), the rates of anxiety and depressive disorders can go up to 66.4 and 34.7%, respectively (7). During remission, rates are lower but still substantial (anxiety: 28.2%; depression: 19.9%), contrasting with rates presented by individuals from the general population (anxiety: 9.6%; depression: 13.4%) (7). Furthermore, depression contributes to disease activity, being associated with more aggressive IBD symptomatology (8). This effect is produced through depression's association with poor disease self-management and increased immune system activation (9, 10). Increased inflammation and disease symptomatology, in turn, increase depression levels (9). However, the overlap and bidirectionality between IBD and depression is still vaguely considered in IBD treatment, and depression has been reported to be underrecognized and undertreated in IBD (9, 11).

Findings from recent studies examining which factors are linked to poor mental health outcomes in people with IBD have suggested that this population may benefit from psychological interventions focused on promoting acceptance and cultivating self-compassion (12–15). Arguments for interventions based on psychological flexibility lie on studies showing the detrimental effects of experiential avoidance (i.e., unwillingness to have internal experiences such as thoughts, emotions, and physical sensations, consequently leading to attempts to avoid them) (16) and cognitive fusion (entanglement with thoughts which leads to taking them as literal truths) (17), on mental health and quality of life outcomes. In people with IBD, cognitive fusion was shown to longitudinally influence changes on perceived physical and psychological well-being for 18 months, over and above IBD symptomatology's influence (13), and to longitudinally predict depression symptoms (18). Additionally, fusion with distressing IBD-related thoughts is linked with lower psychological health and may explain the effects of painful experiences such as shame on this outcome (14). Experiential avoidance, in turn, seems to mediate the effects of IBD symptomatology on well-being and mental health indicators (19, 20). Altogether, these studies indicate that fusion with negative thoughts and attempts at controlling or avoiding internal experiences appear to increase the suffering experienced by people with IBD and potentially contribute to the effects of painful IBD-related experiences on psychological distress. Therefore, the testing of psychological approaches aiming at improving psychological flexibility for better living with this condition is of paramount relevance.

Acceptance and Commitment Therapy [ACT] (16) uses acceptance, defusion, and mindfulness processes, allied with commitment and behavior change techniques, to produce greater psychological flexibility. ACT has been tested in several contexts for the past two decades, with current empirical evidence showing that it is generally superior to inactive controls, treatment as usual (TAU), and most active intervention conditions for anxiety, depression, substance use, pain, and transdiagnostic groups (21). A systematic review examining ACT's use in chronic medical conditions found, nonetheless, that although ACT shows promise, it is not yet a well-established intervention for these populations, recommending that more trials should be conducted (22). The emerging evidence of ACT in addressing symptoms and mental health issues in gastrointestinal disorders has been highlighted (23), and ACT is regarded by people with IBD and health professionals as a helpful approach, especially shortly after diagnosis (24). Nevertheless, to our current knowledge, only one Randomized Controlled Trial (RCT) has been performed in the IBD population. This study showed that an 8-week ACT intervention was superior to TAU in improving stress, depression, and general well-being (25). Nonetheless, several mindfulness-based interventions have been tested in IBD, with results showing efficacy in improving symptoms management (26), fatigue, psychosocial functioning (27), and inflammatory biomarkers (28). Although ACT incorporates mindfulness as a core element in promoting contact with the present moment, it does so in a strictly behavioral approach (29), rather than in its entire philosophical and ethical dimensions (30), and it also includes other techniques for defusion, acceptance, and for promoting values-based action.

Recently, a few studies have called for the pertinence of adding compassion-based components to such interventions based on the fact that people with IBD are impacted by stigma, shame, and self-criticism (12, 15, 31). Concerns of people with IBD can include being treated as different, being ostracized by society, or feeling a burden to others (32, 33). IBD characteristics such as the gastrointestinal nature of symptoms, the chronic and relapsing disease course, and concealability, as well as the historical view of it being a psychosomatic condition make IBD prone to stigmatization (34, 35). The stigmatization of IBD, in turn, is known to impact quality of life, psychological functioning, and treatment adherence (12). Illness-related shame in people with IBD also seems to negatively influence psychological health and quality of social relationships (31). People with IBD may be self-critical, perceiving themselves as inadequate, flawed, or defective, which seems to exacerbate the effects of IBD symptom perception and illness shame on depressive symptomatology (15).

The efficacy of interventions that incorporate compassion cultivation in decreasing psychological distress and psychopathological symptoms, and improving quality of life and well-being, has gained growing evidence (36). Developing self-compassion (i.e., sensitivity to personal suffering and a motivation to alleviate and prevent it in a self-kind and courageous manner) (37) seems to be especially useful to tackle shame and self-criticism (38). Self-compassion is operated through different brain systems than self-criticism (39). It is suggested to be rooted in a soothing-affiliative affect regulation system that counteracts threat-focused emotional responses and cognitive patterns, such as depression, anxiety, shame, and self-criticism (40). In line with this, a recent longitudinal study in people with IBD showed self-compassion to be a protective factor to the experience of stress, depressive symptoms, and anxiety (41). Interventions that promote self-compassion are feasible (42) and present promising results in the context of chronic illnesses, such as persistent pain (43), acquired brain injury (44), and chronic skin conditions (45). Although these data seem to indicate that helping cultivate self-compassion may be useful in IBD, no compassion-based intervention has yet been tested in this population.

The integration of self-compassion components in ACT and mindfulness-based interventions has been an emerging research topic during the past decade. These approaches are considered to be compatible and complementary (46–48). Their integration may have added benefits and appears to be feasible and effective in improving quality of life, experiential avoidance, shame, or self-criticism in populations such as men with HIV (49), women with binge eating (BEfree intervention) (50), obesity (Kg-Free intervention) (51), and breast cancer (Mind programme) (52).

Taking into consideration the high mental health burden of IBD, the pertinence of targeting experiential avoidance, cognitive fusion, shame, and self-criticism in this population, and the feasibility of integrating ACT and compassion-based interventions, it is the aim of the current project to test the efficacy of such integrative intervention tailored to IBD.

### Aims of this Study

This study aims to conduct a two-arm RCT to test the efficacy of a new integrative ACT and compassion-based intervention, the Living with Intention, Fullness, and Engagement with Inflammatory Bowel Disease (LIFEwithIBD) intervention, which was adapted from the Mind programme for people with cancer (52) to the IBD context. This intervention (LIFEwithIBD + TAU)'s superiority in improving psychological distress (primary outcome), quality of life, work and social functioning, IBD symptom perception, illness-related shame, psychological flexibility, self-compassion, disease activity, inflammation biomarkers, and gut microbiota diversity will be compared to TAU.

The contents of the LIFEwithIBD intervention and the design of the RCT are presented in this paper.

## Methods and Analysis

This trial is registered at ClinicalTrials.gov (Identifier: NCT03840707, date assigned 13/02/2019). The planning and implementation were carried out per ethical recommendations outlined by the American Psychological Association (53) and the World Medical Association's Declaration of Helsinki (54). Authorization for sample recruitment was obtained from the Portuguese Data Protection Authority (reference number 3461/2017, 2017-03-24) and the Research Ethics Committees of the Coimbra Hospital and Universitary Center (CHUC).

### Participant Recruitment

Participants were recruited among outpatients from the IBD clinic of the Gastroenterology Service of the CHUC between June and September 2019. Patients were invited to participate in the study by their IBD physician during a scheduled appointment, after assessment by the physician of exclusion criteria (a) (see below). Then, patients were screened by a psychologist through a short interview (to present the project, obtain informed consent, and assess eligibility).

#### Participant Selection

Inclusion criteria were: (a) 18 to 65 years old; (b) being able to read and write Portuguese; (c) having an IBD diagnosis for at least 6 months; (d) being able to give informed consent. Exclusion criteria were: (a) having started a new treatment for IBD in the previous 6 months (in the case of anti-TNF and immunosuppressive therapy) or 2 months (in the case of steroid or aminosalicylate therapy); (b) presenting a diagnosed psychiatric disorder (major depressive disorder, psychotic disorder, bipolar disorder, substance abuse), severe depression, or suicidal ideation (assessed by the Patient Health Questionnaire-9 [PHQ-9 (55)])^1^; (c) undergoing any other form of psychological intervention; (d) being pregnant. Patients non-eligible due to criteria (b) were referred to national mental healthcare services.

### Sample Size

An *a priori* power analysis for this study was performed. In the absence of meta-analytic evidence, we have used data from Wynne et al. (25). Large reductions in mood symptoms were reported at follow-up for depression [*SMD* = 0.88 (0.557–1.21)], anxiety [*SMD* = 0.75 (0.423–1.068)], and stress [*SMD* = 1.1 (0.88–1.559)], even after adjustment for baseline values. Using the smallest of these effect estimates (anxiety), the inclusion of the baseline values as a covariate, an alpha of 0.05 and 80% power, we estimate that a total sample size of *n* = 58 would be required to power the primary analysis.

### Randomization of Participants

Figure 1 shows the flow of participants through the study. Of the 355 patients screened, 279 were excluded for not meeting criteria to participate. Seventy-six participants were randomly assigned to one of two conditions: experimental group (Treatment as Usual + LIFEwithIBD intervention: *n* = 38) or control group (TAU: *n* = 38), through computed-based randomization (www.random.org/lists/). Before the start of the intervention, all participants were contacted by phone. In this process, 6 patients self-excluded from the study due to a lack of resources to attend the sessions (e.g., lack of time, transportation).

**Figure 1 F1:**
[figure not shown]
Diagram of participant enrolment. ^*^included in Intent-to-treat Analyses.

### The LIFEwithIBD Intervention

The LIFEwithIBD intervention is an adaptation of the Mind programme for people with cancer (52), an acceptance, mindfulness, and compassion-based intervention designed to be delivered in a group format, with 8 weekly sessions. The Mind programme was adapted by the psychology members of the current research team for the IBD context, considering the psychological literature in this population. The results and experience derived from the Mind's pilot study and preliminary results (52) were also considered. An extra session regarding educational aspects of IBD was added, modules on shame and self-criticism were further developed, and a gratitude module replaced the forgiveness module of the Mind programme. The module on ACT's observing self was also removed, and some compassion approaches (e.g., Compassionate Image exercise) were replaced by exercises from the Mindful Self-Compassion programme (56).

The LIFEwithIBD is a manualized, group-based intervention comprising 9 weekly sessions, of about 2 h each, to be delivered to people with IBD by certified therapists with clinical experience in ACT and compassion-based interventions. Between-session assignments (usually involving meditative practices with audio guides recorded for this intervention), to be individually performed by participants ideally on a daily basis, are also included in the intervention.

Overall, the LIFEwithIBD intervention focuses on ACT topics such as acceptance of internal experiences, willingness, values, and committed action (16), as well as on mindfulness practice (57), explicit compassion-based approaches [such as Mindful Self-Compassion (56), Compassion-Focused Therapy (58), and Loving Kindness meditation (Buddhist mettā meditation) (59)], and gratitude (especially toward one's body) (59). The intervention also includes educational aspects on IBD and fatigue. In each session, participants are invited to complete experiential exercises, mindfulness and compassion meditation practices, and to discuss in small groups to share their experiences. The LIFEwithIBD first session is intended to present the intervention's aims and structure, allow participants to introduce themselves, have a sense of common areas of suffering, foster creative hopelessness, and offer mindfulness as a different way of facing difficulties. In this session, the Participants' Manual encompassing information to complement the sessions and exercises is provided to each participant. The following sessions, although focusing on different topics, have a similar structure: each session begins with a scripted meditation (some of the scripts adapted to embrace IBD specificities), a review of participants' between-session assignments (whether they encountered obstacles to the practices/exercises, what their experience was like, whether they have discovered something new, etc.), an introduction to the session's topics and in-session experiential exercises (real-life examples and metaphors are designed to facilitate the participants' practice and reinforcement of engaging in the skill addressed in the session), and ends with a mindfulness or compassion meditation practice. The between-session assignments align with the topics explored in each session and include informal practices aiming to integrate mindful awareness in everyday activities. The last session encompasses an extension of committed action (already covered in session 5), focusing on overcoming obstacles, and provides a wrap-up of the intervention, highlighting the role of psychological processes. An overview of the intervention is presented in Table 1.

**Table 1 T1:** Overview of the LIFEwithIBD intervention.

**Session**	**Topics**	**In-session exercises/metaphors**	**Between session assignments**
1: Introduction to the programme and promotion of creative hopelessness	- Presentation of the general aims and structure of the intervention - Identification of areas of suffering and promotion of creative hopelessness - Mindfulness as an alternative strategy to deal with difficulties - The science backing mindfulness	- Introduction to mindfulness: Eating a raisin	- Informal mindfulness
2: Education about inflammatory bowel disease	- Education about inflammatory bowel disease (exploring myths, and common fears and worries) - Introduction to mindful breathing	- 3-min breathing space - Mindful Breathing	- Informal mindfulness - 3-min breathing space - Mindful Breathing
3: Body	- How our evolutionary past influences our mind - The mind-body connection - Physiological responses to emotions - Promotion of awareness of physical sensations	- Notice 5 things - Body Scan	- Informal mindfulness - Body Scan
4: Values clarification	- Clarification and definition of life values - Individual assessment of the alignment between behavior and values' importance	- 80th birthday party (values clarification) - Bull's eye exercise - Passengers on the bus metaphor - Mindfulness of sounds and thoughts	- Informal mindfulness - Mindfulness of sounds and thoughts - Getting in touch with an old friend
5: Committed action and Self-care	- Identification of objectives and obstacles to committed action - Self-care: why it is essential and how to engage in it - Education on fatigue: strategies to cope with different types of fatigue (physical and mental fatigue)	- The spoon theory - 3-min breathing space	- Informal mindfulness - 3-min breathing space - Listing of possible self-care actions
6: Compassion	- Psycho-education on shame and self-criticism - IBD as an invisible disease and IBD-related stigma - Introduction to compassion - Compassion as a strategy to manage difficult feelings and general suffering; Tacking self-criticism with self-kindness - Self-compassion and relaxation training	- Soothing rhythm breathing (58) - Loving-Kindness meditation^a^ (compassion is given to a person we love, an acquaintance, a person with whom we have minor issues, and all people with IBD)	- Informal mindfulness - Soothing rhythm breathing and Loving-Kindness
7: Acceptance and Cognitive defusion	- The power of thinking - Promotion of cognitive defusion - Promotion of acceptance and willingness through cognitive defusion	- Mindfulness practice (body, sounds and breath) - “I am… I am having the thought that I am…” exercise - Exercise “Inviting a difficulty”	- Informal mindfulness - Try on somewhat uncomfortable activities (e.g., go to the cinema without choosing the movie, sit in a different chair) to notice and embrace the feelings of discomfort that arise - Mindfulness of sounds and thoughts and/or Body Scan
8: Compassion and gratitude toward the body	- Continuation of compassionate training - The importance of gratitude for mental health - Promotion of compassion and gratitude toward our body	- Loving Kindness^a^ - Gratitude Meditation^a^ (59) - Supportive touch (56) - 3-min breathing space	- Informal mindfulness - “Ten fingers of gratitude” (60) - Compassionate Body Scan (56)
9: Committed action (continuation)/Intervention summary	- Engaging in committed action: Strategies to overcome expected obstacles - Summary of the intervention: How the promoted psychological processes are connected are interact with each other	- Obstacles in the river exercise (61) - The gardening metaphor	

*Every session starts and ends with a contemplative exercise, except for session. Exercises added in the LIFEwithIBD adaptation are cited. The remaining exercises' citations can be found in the Mind programme's article (52)*.

a *Exercises adapted to the inflammatory bowel disease's context (e.g., with added emphasis in gastrointestinal symptomatology, or on the experience of having an illness)*.

### Intervention Implementation

The LIFEwithIBD intervention was delivered to the experimental group (*n* = 32) through three groups of 11, 12, and 9 participants. Two facilitators delivered the intervention to each group, presenting the content, leading experiential exercises, and facilitating the topics' discussion. The facilitators informed the participants that they could get in contact between the sessions in case they had any queries about the sessions' contents, as recommended by the British Psychological Society (62). Facilitators highlighted the importance of at-home practice, which was reinforced by weekly email reminders. Each week, participants provided a subjective evaluation of each session (e.g., usefulness; the importance of the topic) and the frequency of at-home practice. Participants with three consecutive absences or who attended less than two-thirds of the intervention were considered non-completers. Simultaneously, all participants also received TAU [medical treatment for IBD as recommended by the European Crohn's and Colitis Organisation's guidelines (63), which can include pharmacological and/or surgical treatment].

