### Data Analysis

All analyses are planned as intent-to-treat (ITT). The primary outcome will be the psychological distress (DASS-21–*depression, anxiety, and stress*) measured at 8 weeks (immediately post-intervention) between the two intervention groups and adjusting for baseline scores using ANCOVA. We will examine the ANCOVA's assumptions through standard tests and residual plots and perform transformations. The magnitude of the differences between-treatment groups will be expressed as the standardized mean difference.

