## Discussion

Among those designed for or tested in IBD, the LIFEwithIBD intervention is the first to integrate ACT and compassion approaches. The RCT presented in this protocol paper will provide evidence on the efficacy of this intervention (which was delivered along with TAU) in improving health outcomes in comparison to the exclusive delivery of TAU (medical treatment). Due to the inactive nature of the control condition, future studies should compare the intervention's efficacy to other conditions such as active controls (e.g., psychoeducation) and other psychological interventions tested in IBD, such as Cognitive and Behavioral Therapy (86) or Hypnotherapy (87). The use of an inactive control will indeed be a significant limitation to this RCT, especially considering that participants allocated to this condition were aware of their non-allocation to the intervention group, which may influence answers to the administered self-report questionnaires. Also, contact with a group of people with the same pathology, as well as with the therapists, may in itself provide therapeutic effects only experienced by the experimental group, which adds to the disparity between the study groups. Nevertheless, considering this is the first time the LIFEwithIBD intervention will be tested, the use of an inactive control may provide useful preliminary results on the effects of the intervention.

The greatest limitation to this RCT appears to be participant retention, similarly to previous RCTs testing group interventions in this population, which also showed large attrition rates (25, 86). In the current study this may have been due to participants not being compensated for their participation besides receiving the intervention. Results from this RCT will act as support for future studies testing the LIFEwithIBD intervention or other acceptance and/or compassion-based interventions for IBD.

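### Therapy is delivered in three groups in one arm only, but the sample size and the primary ANCOVA treat all patients as independent, so the primary standard error may be too small

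*Protocol article*

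**What the plan says.** The intervention section describes LIFEwithIBD as a manualised group programme of nine weekly sessions, with discussion in small groups. Under Intervention Implementation, the 32 experimental patients received it "through three groups of 11, 12, and 9 participants", with two facilitators per group. Controls received treatment as usual only.

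The Sample Size section takes the smallest of three effect sizes from an earlier trial (anxiety, standardised mean difference 0.75). It assumes "an alpha of 0.05 and 80% power" with baseline as a covariate, and concludes that "58 would be required to power the primary analysis". It gives no ICC, group size or design effect.

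The Data Analysis section fixes the primary comparison as one "between the two intervention groups and adjusting for baseline scores using ANCOVA". Secondary Analyses uses the same ANCOVA. Longitudinal Outcomes uses mixed models for repeated measures with a group-by-time interaction. No therapy-group term is named in any of these sections, and clustering is not mentioned.

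**The concern.** Patients in the same therapy group share sessions, discussion, peers and facilitators, so their outcomes may resemble each other more than those of patients in different groups. Controls have no such structure. A patient-level ANCOVA attributes all residual variation to independent patients. It does not allow for the fact that the experimental mean rests on only three groups.

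The Discussion makes such correlation plausible. It says that "contact with a group of people with the same pathology, as well as with the therapists, may in itself provide therapeutic effects". The authors raise this about the inactive control, not about clustering, and an equal benefit in every group would create no correlation. But if group and therapist contact affects self-reported distress, it may well do so to a different extent in different groups.

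At stake is the single primary test. If one group went unusually well, an interval that is too narrow could present this as efficacy of the intervention.

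**Working it through.** **Inputs.** Standardised difference 0.75, alpha 0.05, power 80%, one baseline covariate and N = 58 (Sample Size). Therapy groups of 11, 12 and 9, so 32 experimental patients (Intervention Implementation). 61 patients with baseline data (Abstract), so 61 − 32 = 29 controls; this is derived, because the flow diagram is not shown. The ICC is not in the documents, and the values below are assumptions.

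**Reproducing 58.** A two-sided noncentral t with 29 per arm gives 80.1% power at 0.75. An ANCOVA F test with effect size f = 0.375, one covariate and N = 58 also gives 80.1%, and N = 57 gives 79.4%. So 58 is exactly the figure for independent patients and holds no allowance for clustering.

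**Variance with clustering in one arm.** The effective group size is (11² + 12² + 9²)/32 = 346/32 = 10.81. The design effect in the LIFEwithIBD arm is DE = 1 + 9.81 × ICC; the controls have none. On a unit-variance scale:

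- ANCOVA variance of the difference: 1/32 + 1/29 = 0.0657
- True variance: DE/32 + 1/29
- Example at ICC 0.05: DE = 1.491, so 1.491/32 + 1/29 = 0.0811. The ratio is 0.0811/0.0657 = 1.23, and its square root is 1.11.

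**Size of the nominal 5% test:** 2 × [1 − Φ(1.96 / SE ratio)].

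**Power at a true 5% level with the ICC known:** noncentral t, 58 degrees of freedom, noncentrality 0.75/√(true variance).

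| Assumed ICC | DE | Variance ratio | SE ratio | Size of nominal 5% test | Power, 32 vs 29 |
|---|---|---|---|---|---|
| 0 | 1.000 | 1.00 | 1.00 | 5.0% | 82.0% |
| 0.01 | 1.098 | 1.05 | 1.02 | 5.5% | 80.3% |
| 0.02 | 1.196 | 1.09 | 1.05 | 6.1% | 78.6% |
| 0.05 | 1.491 | 1.23 | 1.11 | 7.8% | 73.6% |
| 0.10 | 1.981 | 1.47 | 1.21 | 10.6% | 66.1% |

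A simulation of the unadjusted two-sample test (40,000 runs) gave rejection rates under the null of 5.5%, 8.0% and 10.8% at ICC 0.01, 0.05 and 0.10, in line with the formula.

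**If the group variance must be estimated.** Three groups leave two degrees of freedom between groups. With v₁ = DE/32 and v₂ = 1/29, the Satterthwaite value is (v₁ + v₂)² / (v₁²/2 + v₂²/28). At ICC 0.05 this is 0.0811² / (0.0466²/2 + 0.0345²/28), or about 5.8, and power is about 59%. Even at ICC 0 the same test has about 8.1 degrees of freedom and 73% power, so much of this loss comes from having only three groups.

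**What the planned ANCOVA itself would do.** At a true difference of 0.75, the simulated rejection rate of the unadjusted test was 82%, 80% and 78% at ICC 0, 0.05 and 0.10. The planned test therefore still rejects at close to the stated rate. The harm appears as excess false positives and a narrow interval.

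**The case against.** The strongest objection is that everything depends on an ICC that the documents do not give. At 0.01 or below, less than two percentage points of power are lost and the test size stays near 5.5%. A therapist manual and trained, certified facilitators (Treatment Integrity) may limit variation due to facilitators, though not peer effects. This stands, and it is why the point is conditional.

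A reader might infer that the standard error is definitely too small and that 80% power is not delivered. The documents do not support that. With 61 analysed, size-corrected power is still 80.3% at ICC 0.01, and the planned ANCOVA keeps a rejection rate of roughly 78% to 82% for ICCs up to 0.10. The shortfall in power arises only for a test held to a true 5% level.

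A reader might also infer that the longitudinal models assume independent patients. That section states no covariance or random-effects structure; all that can be said is that no therapy-group term is named. Nor can a power loss from dropout be added here. Retention is called the greatest limitation, but no loss rate at the primary time point is given.

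If 0.75 is an unadjusted effect, correlation with baseline could recover some power. None is stated, 58 takes no credit for one, and it would not by itself correct the false-positive rate.

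Finally, recruitment and delivery are complete, so neither the patient number nor the number of groups can change. That limits the remedy to analysis and reporting but does not remove the need for it. Nor is this a detail left to an analysis plan, because the article itself fixes the sample size and the primary model.

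**Conclusion.** The point holds in conditional form. Group delivery in one arm is a fact of the design, 58 is the independent-patient figure, and the primary ANCOVA as written carries no therapy-group term. For any positive within-group correlation, its standard error is too small.

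Under assumed ICCs of 0.02 to 0.10, with 32 versus 29 analysed, the true standard error is about 5% to 21% larger than the reported one and the real test size is about 6% to 11%. These figures rest on the assumed ICCs, the derived 29 controls, complete data on all 61 patients and equal total variance in both arms.

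**What to change.** In the primary analysis, account for therapy group in the LIFEwithIBD arm only, and carry the same into the longitudinal models:

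- Fit a model with a random intercept for therapy group in the experimental arm and small-sample degrees of freedom (Satterthwaite or Kenward-Roger).
- Because three groups cannot estimate this variance reliably, report alongside it the primary estimate with its standard error inflated at fixed ICCs of 0.02, 0.05 and 0.10. With 32 versus 29 the multipliers are 1.05, 1.11 and 1.21; recompute them from the numbers actually analysed.
- State in the Sample Size section that 80% power assumes no clustering. With 61 analysed and a fixed ICC, power at a true 5% level is about 79%, 74% and 66% at ICC 0.02, 0.05 and 0.10. It is about 59% at ICC 0.05 if the variance is estimated with about 6 Satterthwaite degrees of freedom. Label the ICCs as assumptions.

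The cost is a little extra analysis, with no new data because the groups are known from delivery, plus a wider interval and a less favourable stated power.
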